### Cognitive training intervention

The cognitive training intervention consists of a 5-week digital cognitive training and a module promoting a healthy, active lifestyle including psychoeducational information on a healthy, active lifestyle and activity monitoring using a digital activity diary.

#### Computerized multi-domain cognitive training

The computerized training will be delivered by the CE-certified class-I medical device “HeadApp/NEUROvitalis Digital” (HelferApp GmbH, https://start-headapp.helferservices.net) offering adaptive, multi-domain cognitive training accessible from home with internet access. Participants will train for a total of 15 training sessions across 5 weeks, 40 min per day, three times a week resulting in a total training duration of 600 min, which is comparable to previously published interventions [34]. The training consists of six different tasks addressing one primary cognitive domain each: executive functions, working memory, episodic memory, attention, visuo-cognition, and language. The training starts with the lowest difficulty and adapts to training performance concerning higher difficulty and task complexity levels. With higher difficulty levels, all tasks involve a strong executive component, leading to a strong executive focus of the applied cognitive training. The training tasks are based on the scientifically validated NEUROvitalis program (ProLog, Therapie und Lernmittel GmbH, Cologne) [65–69]. Depending on their group assignment, participants receive their login credentials and information about the training during their t0 or t2 visit. The training will be monitored weekly on the HeadApp/NEUROvitalis Digital website by the individual’s contact person, and any queries of participants will be answered by telephone or email, depending on the participant’s choice.

#### Healthy lifestyle information

The intervention is enriched by psychoeducation promoting a healthy, active lifestyle. Topics include risk and protective factors of healthy aging, cognitive and motor reserve, advice for incorporating more cognitive, physical, and social lifestyle activities into daily life routines, the influence of diet on (cognitive) health, and information on the Mediterranean diet. A graphic booklet will deliver the healthy lifestyle information to the participants at the beginning of the intervention period, i.e., at the t0 or the t2 visit. The psychoeducation booklet is based on the scientifically validated NEUROvitalis program (ProLog, Therapie und Lernmittel GmbH, Cologne) [65–69].

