## Methods/design

### Study design and setting

The study CogTrAiL-RBD is designed as a monocentric, single-blinded, delayed-start randomized controlled trial with two study arms aiming to consecutively recruit 80 individuals with iRBD confirmed by polysomnography from the continuously expanding local iRBD cohort at the University Hospital Cologne in Germany [54]. Participants will be randomly assigned to either the early intervention group or a delayed-start control group. Forty participants will be randomly assigned to each group (parallel group phase, superiority). The delayed-start control group will receive the same intervention after a 6-month waiting period, with the early intervention group undergoing the intervention for a second time to separate symptomatic from potentially disease-modifying effects (open-label phase, exploratory) [55].

Figure A-1 presents the schematic trial design and Appendix Figure A-1 further illustrates the timeline for participants. At baseline assessment (t0, week 0), the study will be explained to the participants. Subsequently, the participants will provide written informed consent and answer to a demographic interview. All participants with iRBD will undergo comprehensive clinical and neuropsychological assessments at the t0 visit and 6 weeks post allocation (posttest I, t1, week 6). A follow-up assessment (follow-up I, t2, week 33) will be conducted after 6 months. Subsequently, the second intervention phase for both the early intervention group and the delayed-start control group begins, followed by another clinical and neuropsychological assessment (posttest II, t3, week 39). Finally, a follow-up assessment (follow-up II, t4, week 66) will take place after an additional 6 months.

There are three optional study modules for individuals with iRBD that accompany the mandatory clinical and neuropsychological assessments: (i) the MRI module consisting of structural and functional MRI at each assessment time point; (ii) the accelerometry module consisting of physical activity tracking with accelerometers at each assessment time point; and (iii) the polysomnography module including two polysomnographies, one before the start of the intervention and one within the last 2 weeks of the intervention. Additionally, an age- and sex-matched HC group will be examined at the first assessment time point, participating in the comprehensive clinical and neuropsychological assessments, the MRI module and the accelerometry module.

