#### Weekly/monthly activity diary

During the study, participants of the early intervention group will fill out weekly (between t0 and t1, t2 and t3) and monthly (between t1 and t2, t3 and t4) digital activity diaries, reporting their cognitive and social lifestyle activities, physical activity level, and Mediterranean diet adherence. Participants of the delayed-start control group will fill out the weekly and monthly digital activity diaries following their introduction to the training following the t2 visit. With this monitoring, we aim at a continuous reflection of activity levels in the domains of the psychoeducational program of participants, motivating the implementation of new active daily life routines. To assess these lifestyle activities, we use established, validated questionnaires. The short version of the International Physical Activities Questionnaire (IPAQ) [70, 71] is used to assess physical activity levels, cognitive and social lifestyle activities are assessed with the Lifestyle Activities Questionnaire (LAQ) [72, 73], and adherence to the Mediterranean diet with the Mediterranean Diet Adherence Screener (MEDAS) [74, 75]. In the weekly version of the activity diary, the questions refer to the past week and in the monthly version they are related to the past month. For each lifestyle domain (cognitive and social lifestyle activities, physical activity, and Mediterranean diet adherence), we additionally ask for subjective ratings of the participant’s activity level in general and compared to the past week/the past month on a 4-point Likert scale. The activity diary questionnaires are sent out by email via SoSci Survey (SoSci Survey GmbH, Munich, Germany). Mailing lists are generated in *R* and directly uploaded to SoSci Survey to automatically send out individualized links to fill out the activity diaries at the planned time points.

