#### Neuropsychology and motor assessments

All subjects will undergo clinical and neuropsychological assessments, including paper–pencil cognitive and motor evaluations. The in-person assessments take around 2.5 h to complete, including a short break according to the participant’s needs. The test battery will be administered by psychologists or graduate students of Psychology or Medicine at all time points. The outcome assessors will be thoroughly trained in administering and scoring the assessments. Following the in-person assessments, participants digitally fill out questionnaires on various non-motor symptoms, quality of life, and lifestyle activities, which are sent to them via SoSci Survey (SoSci Survey GmbH, Munich, Germany). An automatic reminder email is sent to the participants, if they do not complete the questionnaire within 1 week of their study visit. A complete list of all cognitive assessments, motor evaluations, and questionnaires, including references, is presented in Table 1. Parallel test forms are used if available (i.e., alternating between time points). Test scores are standardized into *z*-scores, percentage ranks (PR), or *T*-scores using published normative data, as available. All evaluations are double-checked and digitalized using the four-eye principle. All standardized scores are transformed into *z*-scores during data preprocessing to create the domain composite scores. Table 1 provides an overview of the assignment of cognitive tests to the respective domains.

**Table 1 Tab1:** Neuropsychological and motor assessments in CogTrAiL-RBD

Domain	Abbreviation	Assessment	Reference	Baseline	Posttest I and II	Follow-up I and II

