#### Accelerometry: physical activity tracking

All willing participants will be asked to wear a wrist-mounted movement sensor measuring linear acceleration and angular velocity on their dominant hand for 7 days around each assessment time point. The sensors will be distributed either during the assessment session (along with a prepaid return envelope) or sent to the participants 10 days prior the next assessment. The participants will be instructed to wear the sensor as much as possible throughout their days and nights. Additionally, participants will be asked to fill out a diary noting their bedtimes, daily activities, and periods when they are not wearing the device.

The CE-certified movement sensor used in this study is the AX6 from Axivity Ltd, Newcastle upon Tyne, England. Detailed information about the AX6 and the wrist strap can be found in the Data Sheet documents available on the Axivity website (https://axivity.com/product/ax6). The sensors will be configured to record data continuously for 7 consecutive days and nights (168 h) at a sampling rate of 100 Hz with an accelerometer range of ± 8 g. Sensor set-up and data storage will be managed using the open source AX3/AX6 OMGUI Configuration and Analysis Tool (https://github.com/digitalinteraction/openmovement/wiki/AX3-GUI). Data retrieval from the sensor is only possible via a USB cable connection. Data will be saved in the Continuous Wave Accelerometer (*.cwa) binary format containing the raw actigraphy data, metadata, and device configurations.

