#### Magnetic resonance imaging

Extensive brain imaging with a 3 T SIEMENS PRISMA scanner equipped with a 64-channel head coil will be conducted at the Research Center Jülich near Cologne for all willing participants at all time points (t0–t4). The MRI scanning will preferably occur within 7 days of the clinical and neuropsychological assessment. However, in case of technical difficulties with the scanner or timing issues with the participants (e.g., illness or personal reasons), it may be conducted up to 3 weeks apart. During MRI measurements, at least one member of the study team is present. This person will be supported either by another member of the study team or by a medical-technical radiology assistant of the Research Center Jülich. The net scanning time for all sequences lasts 69:33 min. The sequences, their features and specifications, spatial resolution, repetition times (TR), and echo times (TE) as the basic pulse sequence parameters are described in Table 2. The MRI data will be exported and saved in the DICOM format (*.dcm).

**Table 2 Tab2:** Magnetic resonance imaging protocol CogTrAiL-RBD

Sequence	Features	Duration
T1-weighted	The T1-weighted sequence will be used to monitor cortical thickness, gray matter volume, and deformation. These metrics are well-established markers which might change upon training. Sequence parameters: 0.9 mm isotropic MP2RAGE, TR 2500.0 ms, TE 2.22 ms	6:24 min
Neuromelanin-sensitive turbo spin echo	Turbo spin-echo (TSE) sequences allow for contrast evaluation of neuromelanin containing structures, i.e., locus coeruleus and substantia nigra. Measures of locus coeruleus integrity like volume, voxels with highest intensity as well as contrasts of spatial subdivisions will be performed [111]. Such measures will elucidate the role of an intact locus coeruleus as prerequisite for successful cognitive training. Sequence parameters: 0.4 × 0.4 × 1.8 mm^3^ resolution, TR 825.0 ms, TE 18.00 ms	7 × 2:24 min = 16:48 min

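### At t2 the delayed-start arm gets its intervention material at the visit, but the t2 questionnaires, sensor week and MRI can follow, so its last untreated values may not be untreated

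*Protocol article*

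**What the plan says.** **Hand-over at t2 (Protocol article).** Under Computerized multi-domain cognitive training, "participants receive their login credentials and information about the training during their t0 or t2 visit", according to group. Under Healthy lifestyle information: "A graphic booklet will deliver the healthy lifestyle information to the participants at the beginning of the intervention period, i.e., at the t0 or the" (for this arm, t2). Under Weekly/monthly activity diary, delayed-start participants "will fill out the weekly and monthly digital activity diaries following their introduction to the training following the t2 visit". Under Study design and setting, once the t2 assessment has been described: "Subsequently, the second intervention phase for both the early intervention group and the delayed-start control group begins".

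**Collection of t2 data.**
- Questionnaires on non-motor symptoms, quality of life and lifestyle are completed online after the in-person session. The only timing control stated is this: "An automatic reminder email is sent to the participants, if they do not complete the questionnaire within 1 week of their study visit". No closing date is given.
- Accelerometry covers a 7-day span at every visit, and two routes are given for the device: "The sensors will be distributed either during the assessment session (along with a prepaid return envelope) or sent to the participants 10 days prior the" (the sentence closes by naming the assessment that follows).
- MRI is preferably done within 7 days of the clinical assessment. If there are scanner or scheduling problems, "it may be conducted up to 3 weeks apart". Before or after is not specified.
- Polysomnography is the only module with an explicit order: its first night must precede training.

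**Use of t2.** The Statistical analyses section makes t2 a time level, with t0 and t1, in the mixed models for primary and secondary outcomes. Under Assessments, non-motor symptoms and quality of life are secondary, while accelerometry and imaging are exploratory.

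**The concern.** t2 is the only controlled measurement of the longer-term effect, and it is meant to compare participants who have had the intervention with participants who have had none. The plan ties hand-over to the visit, but lets part of the t2 data be collected after it. Nothing stated makes the hand-over wait for those data.

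The exposure is clearest for self-report. The lifestyle (LAQ), physical activity (IPAQ) and diet (MEDAS) questionnaires ask about the behaviours that the booklet teaches, and the diary uses the same instruments with the stated aim of motivating change. A control participant who answers a few days after the visit may have read the booklet even if no training session has taken place. Quality of life and mood could also respond to finally receiving the intervention.

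Two comparisons would suffer. The between-arm contrast at t2 could become treated versus newly treated. The same t2 value is also the starting value for the delayed arm's own course, so its change to t3 would be measured from a shifted baseline.

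**Working it through.** The sample-size figures play no part in this point. The check is calendar arithmetic on the stated visit weeks, windows and training frequency.

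**Inputs**
- t2 at week 33 and t3 at week 39 (Study design and setting).
- 15 sessions of 40 minutes, 3 per week (Computerized multi-domain cognitive training).
- Questionnaire reminder after 7 days (Neuropsychology and motor assessments).
- Sensor week of 7 days (Accelerometry).
- MRI limit of 21 days (Magnetic resonance imaging).

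**Step 1: slack between t2 and t3.** Interval = 39 − 33 = 6 weeks. Course length = 15 / 3 = 5 weeks. Slack = 6 − 5 = 1 week. The start day of training is not stated, so I assume a lag L of 0 to 1 week after t2.

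**Step 2: sessions completed by day d after t2.** Sessions = 3 × (d/7 − L), not below 0.

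| Day after t2 | L = 0 | L = 1 week | Share of 15 sessions |
|---|---|---|---|
| 7 | 3 × 1 = 3 | 3 × 0 = 0 | 0–20% |
| 14 | 3 × 2 = 6 | 3 × 1 = 3 | 20–40% |
| 21 | 3 × 3 = 9 | 3 × 2 = 6 | 40–60% |

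At day 21 this is 6 × 40 = 240 to 9 × 40 = 360 of 600 minutes. These counts cover training only. The booklet is given at the visit, so any later measurement follows that component whatever L is.

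**Step 3: can the stated calendar absorb a late scan?** A scan 3 weeks after t2 followed by a full course needs 3 + 5 = 8 weeks, and 6 are available. A scan at the late limit therefore falls inside the delayed arm's training unless t3 moves.

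**Step 4: effect on the contrast (illustration only).** Suppose a share f of controls is measured late and has already gained a share g of the full effect. With the early arm left as it is, the contrast becomes d × (1 − f × g). Both f and g are assumptions. The planning value d = 0.5 belongs to the executive composite and is borrowed only for scale.
- f = 0.25, g = 0.2: 0.5 × (1 − 0.05) = 0.475
- f = 0.5, g = 0.4: 0.5 × (1 − 0.20) = 0.40
- f = 1, g = 0.6: 0.5 × (1 − 0.60) = 0.20

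**Step 5: do other statements close the gap?** Study design and setting puts the second phase after the t2 assessment, and the diary section puts the introduction to training after the t2 visit. Both sit awkwardly with hand-over during the visit and should be reconciled with it. Neither says that the questionnaires, sensor week or scan must be finished first.

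**The case against.** The strongest case is that the plan's sequence is assessment first and intervention second, and that holding credentials and a booklet is not the same as being on treatment. No section says that training starts on the visit day. The polysomnography rule implies some delay for controls in that module, since their first night falls after t2 and before training. The late MRI limit is an exception for practical problems, and a scan may equally precede the visit. Sensors can be mailed ahead. Accelerometry and imaging have separate analysis plans that are not shown and may deal with late measurements. An article also condenses the full protocol.

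Much of this stands. It makes the exposure a possibility rather than a certainty, makes 9 of 15 sessions an upper bound, and limits what can be said about the exploratory modules. It does not remove the point for the questionnaires. Their completion after the session and the hand-over at the visit are both stated timings, and the two together allow the wrong order. Nor can an analysis plan undo contamination once it has happened.

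A reader might go further and infer three things that the document does not support:
- **That the primary result is compromised.** The executive composite, like the other cognitive tests and the motor examination, is taken in person at the visit, and nothing shows that it follows the hand-over.
- **That anyone answering after the one-week reminder has completed at least three sessions.** With the week of slack, the count at day 7 is 0 to 3.
- **That the bias must run toward no difference.** That holds for contamination of controls taken alone. The early arm begins its second course at t2 and may shift as well.

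**Conclusion.** The point holds in limited form. As written, the plan allows the delayed-start arm's t2 values to be collected after intervention material is in hand. This applies to secondary self-report outcomes, most clearly LAQ, IPAQ, MEDAS and quality of life, and to exploratory accelerometry and MRI.

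The possible exposure is 0 to 3 of 15 sessions at day 7 and 6 to 9 at the 21-day MRI limit. This rests on training starting 0 to 1 week after t2, at the planned frequency, with t3 held at week 39. How many participants are affected cannot be known from the document, and neither can the net direction of bias. No sample-size figure changes. The point merits correction because secondary outcomes are exposed, the remedy is cheap, and the contamination is not recoverable afterwards.

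**What to change.** **Going forward, at t2:**
- Release booklet, credentials and diary only once the t2 questionnaires are returned, using the roughly one week of slack before t3. The questionnaires can still go out after the visit, so their mode stays the same across time points.
- Use the existing advance-mailing route for the t2 sensor, so that the recording week precedes the hand-over.
- Schedule the t2 MRI before the visit, or before the first training session, where possible. Do not hold the intervention for a late scan: a 3-week wait would leave 6 − 3 = 3 weeks for a 5-week course.
- Reconcile the statements on whether the introduction to training happens during or after the t2 visit.

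**At t0:** apply the same ordering rule, because the early arm's baseline questionnaires, sensor week and scan can likewise follow its hand-over. Consent is given at the t0 visit, so advance mailing of the sensor does not fit there as described, and the order has to come from when the material is released.

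**For participants already past t2:** use completion dates to flag values obtained after hand-over, and report a sensitivity analysis of the t2 contrast. State that excluding late responders selects on behaviour after randomisation. For MRI, with 30 participants at t0 when the article was revised, the remaining set may be small.

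**Cost:** a scheduling instruction, a recorded date and one extra analysis. The second phase starts some days later for a few participants. The change was still worthwhile at the time of the article: 55 of 80 were enrolled, so at least 80 − 55 = 25 had not reached t2.

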#### Weekly/monthly activity diary

During the study, participants of the early intervention group will fill out weekly (between t0 and t1, t2 and t3) and monthly (between t1 and t2, t3 and t4) digital activity diaries, reporting their cognitive and social lifestyle activities, physical activity level, and Mediterranean diet adherence. Participants of the delayed-start control group will fill out the weekly and monthly digital activity diaries following their introduction to the training following the t2 visit. With this monitoring, we aim at a continuous reflection of activity levels in the domains of the psychoeducational program of participants, motivating the implementation of new active daily life routines. To assess these lifestyle activities, we use established, validated questionnaires. The short version of the International Physical Activities Questionnaire (IPAQ) [70, 71] is used to assess physical activity levels, cognitive and social lifestyle activities are assessed with the Lifestyle Activities Questionnaire (LAQ) [72, 73], and adherence to the Mediterranean diet with the Mediterranean Diet Adherence Screener (MEDAS) [74, 75]. In the weekly version of the activity diary, the questions refer to the past week and in the monthly version they are related to the past month. For each lifestyle domain (cognitive and social lifestyle activities, physical activity, and Mediterranean diet adherence), we additionally ask for subjective ratings of the participant’s activity level in general and compared to the past week/the past month on a 4-point Likert scale. The activity diary questionnaires are sent out by email via SoSci Survey (SoSci Survey GmbH, Munich, Germany). Mailing lists are generated in *R* and directly uploaded to SoSci Survey to automatically send out individualized links to fill out the activity diaries at the planned time points.

